## 4. Discussion

Dementia has a complex and multifaceted impact on PLwDs and their caregivers. Unfortunately, in Malaysia, there is a relative lack of awareness and understanding about dementia, which has resulted in stigma and thus created barriers to diagnosis and treatment [2]. This study aims to develop a mobile app to support PLwD caregivers by providing information, facilitating access to nearby health services, maximizing the use of available local resources, and improving caregiving skills. To the best of our knowledge, this is the first mobile app in *Bahasa Malaysia* specifically designed for PLwD caregivers in the local context. 

The recent COVID-19 pandemic fosters digital transformation and adoption across multiple industries and sectors [67]. Evidence shows that the pandemic has increased the global uptake of mobile health apps [22], with more individuals, including older adults, encouraged to improve their health [23]. In the case of dementia, numerous memory clinics have been forced to cease operations due to the COVID-19 pandemic, prompting experts to call for global support for PLwD care [68]. 

We anticipate several challenges while implementing this study. In Phase I, careful planning is crucial for us to complete it within a specific time frame. Scheduling FGDs with clinicians and other field experts can be daunting due to their busy schedules, especially if we plan to conduct a physical session. We foresee the possibility of having to send repeated reminders or conducting one-on-one sessions for those unable to attend the group sessions. Similarly, we need to strike a balance when opting for online or on-site sessions; each has its advantages and disadvantages. NGTs and FGDs also require good communication skills on the moderator’s part to maximize the benefit of the sessions. For instance, the moderator (researcher) needs to know how to handle different group dynamics, prompt participants (to give more feedback), ensure that everybody is heard, and manage disputes or arguments when they occur [39,46,69]. Understandably, these are not easy tasks, if not handled well, they can hamper the data collection process. Likewise, the moderator must exercise caution while asking for feedback and ideas; if there are too many, it may be difficult to screen and narrow down the important and relevant ones. 

The phase of designing and developing the mobile app entails a set of challenges in the intersection between health and digital technology (and its implications)—some of which may not be familiar to healthcare providers and health researchers. For instance, when dealing with any software developer, it is critical to ensure that they are credible, as evidenced by previous successful projects, and capable of meeting the researcher’s requirements for the intended outcome to be achieved [70]. Additionally, it is important not to overlook legislative involvements to safeguard the interests, terms, conditions, and rights of all parties involved, including the researcher, the software developer, and the users [71,72]. This entails a fair agreement on copyrights and intellectual property ownership, data privacy, and how the app should be maintained and used after the completion of the study. Another issue that may arise is the commercialization of the mobile app once it is launched or after the study period. It is incumbent upon the researchers to take this into account in the planning stage and have a clear stand when discussing and negotiating with the software developer. Under normal circumstances, software developer companies are profit-driven business entities; thus, they are likely to have an interest in commercializing the mobile app. 

Researchers, on the other hand, may have different views and values, often with a strong desire to ensure equity and affordability while providing services. Such a discrepancy can sometimes result in tension or disputes. Nevertheless, these “conflicts” are manageable if both parties have a realistic expectation and understanding of each other’s role, values, and interests from the beginning and remain in constant effective communication that ensures a win-win situation. 

Of equal importance is mobile app sustainability in the long run, which again, needs to be part of the study plan. Engaging with a credible mobile app developer is one way of ensuring the utility and longevity of the app, but this requires balancing with other issues like ensuring affordable access and data privacy protection. Collaborations with private or business entities have their own merit but at times can get rather complicated for researchers to handle. In such cases, it is wise for the researcher to obtain legal advice from the legal unit of the academic institution or find alternatives, such as partnering with non-profit entities or software developers from within the academia. 

Another challenge is improving the generalizability of Phase III findings. If the study population is small—meaning the number of PLwD and their caregivers is not practically adequate to allow for a random selection—we may have to employ convenient sampling. However, this method is susceptible to selection bias, as the caregivers selected may not represent the whole caregiver population. To address this issue, universal sampling can be done. Alternatively, we can take additional steps to ensure a diverse sample regarding sociodemographic characteristics (e.g., age, race, education level, and location (urban or rural). 

## 5. Limitations and Strengths

This study has several limitations. First, convenient sampling may render selection bias as discussed earlier, given that our sample is derived from health centers in highly urbanized areas. Second, it is difficult to ensure that caregivers utilize the app frequently (during the trial period) before we assess its usability. However, this can be compensated by regular communication and encouragement. 

On the other hand, the study’s strengths include combining qualitative and quantitative methods with a relatively rigorous process of content development in Phase I. Similarly, this study can be considered unique as it brings together health, caregiving, and digital technology into one sphere—a complex combination that provides rich insight into the future of health research and pushes the boundaries of the roles of a typical health researcher. 

## 6. Conclusions

This protocol describes and elaborates on the steps and processes of developing a mobile app for PLwD caregivers in the Malaysian context. Our findings will contribute to the existing body of knowledge on the interaction between digital health modalities—specifically mobile apps—with caregiving, aging, health, and well-being. Other than that, the study findings will highlight the needs of PLwD caregivers in the local context. The mobile application is expected to be launched and made available to the public through collaborations with other stakeholders, such as senior citizen advocacy groups and the Malaysia Ministry of Health. These partnerships can accelerate the adoption of digital health and technologies in caregiving at the policy level. In addition, the availability of a caregiver mobile app can aid clinicians in managing PLwD by providing caregiver support. 

For future research, we recommend a study to test the effectiveness of this mobile app in reducing caregiver burden and mental stress and improving the QOL of PLwD caregivers. This can be conducted using intervention/experimental designs such as randomized controlled trials or quasi-experimental studies. Another potential research area is the replication of this mobile app in another setting, with some adjustments and modifications to the app. More importantly, we hope to holistically contribute to the betterment of PLwD caregivers by making this tool (app) available and prompting more uptake of digital technology in the field of caregiving while ensuring equity and sustainability.

## Figures and Tables

**Figure 1 ijerph-19-11880-f001:**
[figure not shown]
Overall study flowchart.

**Table 1 ijerph-19-11880-t001:** Example of Nominal Group Technique Voting Scores Template.

Solution/Ideas	Participant 1	Participant 2	Participant 3	Participant 4	Participant 5	NGT Scores
Solution/Idea 1	4	4	5	4	5	22
Solution/Idea 2	2	1	3	2	2	10
Solution/Idea 3	5	5	5	4	4	23
Solution/Idea 4	3	1	5	2	4	15
Solution/Idea 5	4	4	5	4	3	20

**Table 2 ijerph-19-11880-t002:** Inclusion and exclusion criteria in Phase III.

Criteria	Eligibility
**Inclusion**	Primary caregiver of a person living with dementia. A primary caregiver in this study is defined as a person who helps in the personal care of an older adult with dementia, regardless of their education or experience for one month or more during the last 12 months [43,44]. Aged ≥ 18 years old. Caring for an older relative aged ≥ 60 years old diagnosed with any form of dementia. Owns a working and compatible smartphone (Android with mobile data). Has basic knowledge of using smartphones and apps.
**Exclusion**	Not able to communicate independently in English or Bahasa Malaysia. Does not use Android as their mobile operating system.

**Table 3 ijerph-19-11880-t003:** Operational definition of usability and its domains.

Variable/Domain	Operational Definition
**Usability of mobile app**	Usability is determined by the total and mean scores of all domains (ease of use, interface, and usefulness) derived from the M-MAUQ. Higher scores indicate greater usability. A total mean score equal to, or more than, 72 denotes that the app has good usability and vice versa.
**(a) Ease of use**	There are 5 items under this domain. A total mean score equal to, or more than, 20 under indicates that the app is easy to use, and vice versa.
**(b) Interface and satisfaction**	There are 7 items under this domain. A total mean score equal to, or more than, 28 indicates that the app has a good interface and is satisfactory, and vice versa.
**(c) Usefulness**	There are 6 items under this domain. A total mean score equal to, or more than, 24 indicates that the app is useful and serves its purpose and vice versa.

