### 1.3. Research Objectives

The general aim of this study is to develop and assess the usability of “Demensia KITA”, a mobile app for dementia caregivers in Malaysia. Specific objectives include:To develop suitable and relevant content for the mobile application.To develop and design a mobile app prototype that uses the national language (Bahasa Malaysia) as the interface.To determine the usability of the mobile app among PLwD caregivers.

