## 2. Methodology

### Study Design

This research employs a combination of qualitative and quantitative methods and comprises three phases. In Phase I, Focus Group Discussion (FGD) and Nominal Group Technique (NGT) will be used to develop the app content. In Phase II, the mobile app is developed and designed. In Phase III, the usability of the app is tested using the Malay version of the mHealth App Usability Questionnaire (M-MAUQ). 

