**Phase II: Designing of “Demensia KITA”**

Phase II will begin upon completion of phase I. It will entail designing and developing the mobile app, named “Demensia KITA”, with a software developer from within academia specializing in health-related mobile apps.

The preliminary prototype in this phase will be a native mobile application [47] optimized for a specific device and operating system and can be downloaded and installed from a web store (Play Store). It will be free of charge at this stage. Android will be selected as the mobile operating system due to its global dominance [48]. Apart from appropriate typography [49], the prototype aims to incorporate four primary features: rich experience; intuitive; personalized experience; and simplicity [50]. According to Forbes, 14% of smartphone users delete an app that is difficult to use [50]. As a result, easy navigation and overall usability, such as fewer clicks and actions, will be considered to ensure a positive mobile app user experience. The user interface will be as straightforward and intuitive as possible. The prototype version of the mobile app will also function offline, potentially extending reach to underserved populations as internet access is only required for app downloading and software updating. 

Demensia KITA will be fully operated in *Bahasa Malaysia*. The registration process will be personalized and simplified, and users will be able to log in using their personal external accounts such as Google, Facebook, and Twitter. Apart from credible information regarding dementia care, there will be features such as relevant spiritual and cultural practices to keep caregivers motivated and engaged.

Phase II is expected to take approximately one year. The early prototype version will be registered for a one-time fee on Google’s Android (Google Play Store) operating system platform to evaluate its usability. The Alpha version (an early pre-release version that is part of a dedicated testing process) [51] will be tested among 30 dementia caregivers conveniently selected from GHKL and UMMC beforehand to ensure the functionality of the app.

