**Variables and tools**

The usability of a mobile app is defined as the quality attribute that assesses how easy a system interface is for users [56]. Usability generally includes three domains: ease of use, interface and satisfaction, and usefulness. The *ease of use* domain in this study is defined as the extent to which understanding, learning, and operating the mobile app’s specific system or technology is free of physical and mental effort [57,58]. The *interface and user satisfaction* are linked to the convenience of obtaining quality information through the mobile app [59]. Lastly, *usefulness* is defined as the quality of having utility (helpfulness of the mobile app) in serving the intended purpose [60]. 

Usability is measured using the M-MAUQ scale [61]. The mHealth App Usability Questionnaire (MAUQ) was originally developed by Zhou and colleagues to evaluate the usability of mobile health applications among patients and healthcare providers [62]. It came in four versions that assess the type of app (interactive or standalone) and intended audience (patient or health care provider). For this study, the phrase “MAUQ standalone used by patient” is used. The term “patient” here refers to an individual who utilizes a mHealth application to monitor, improve, or manage their health [61,62]. According to Zhou, the questionnaire comprises 18 items and is divided into three subscales: ease of use (five items), interface and satisfaction (seven items), and usefulness (six items). Participants rate each item on a seven-point Likert scale ranging from 1 (strongly disagree) to 7 (strongly agree). App usability is determined by the sum and average of all statements—the higher the average, the better. However, if the average score is less than 4, the app’s usability is poor [61]. The highest possible score is 126, and the lowest is 18. An average score equal to, or greater than 72 indicates that the app is usable. The M-MAUQ questionnaire has been translated into the Malay language and validated among the Malaysian population with a Cronbach alpha of 0.94 [61]. Its content validity indexes (CVI) for relevance and clarity were 0.98 and 0.94, respectively, and the face validity index for understandability was 0.96. For each item in M-MAUQ, the kappa statistic indicated high agreement between raters, ranging from 0.76 to 1.09 [61]. 

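### Phase III admits caregivers who may not read Malay, although the app and its only outcome questionnaire are in Malay

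*Protocol article*

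**What the plan says.** **Eligibility.** The Phase III exclusion in Table 2 of the protocol article reads "Not able to communicate independently in English or Bahasa Malaysia". The other criteria cover caregiver role, age, the care recipient, an Android phone and app familiarity ("Has basic knowledge of using smartphones and apps"). None concerns reading Malay. The caregiver definition applies "regardless of their education or experience for one month or more during the last 12 months", so education does not act as an indirect literacy screen.

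**App.** Section 1.3 sets the objective of a "mobile app prototype that uses the national language (Bahasa Malaysia) as the interface". The Phase II section adds: "Demensia KITA will be fully operated in" Bahasa Malaysia. No English interface is described.

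**Outcome.** Usability is measured with the Malay MAUQ. Under Variables and tools: "The M-MAUQ questionnaire has been translated into the Malay language and validated among the Malaysian population". Data collection has it sent online by e-mail or WhatsApp after four to six weeks of app use. Methods of data management makes every question on the form compulsory. No English form, translation help or analysis by language is described.

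**Decision rule.** Section 3 (Phase III) and Table 3 call usability good if the mean total is at least 72. Table 3 sets domain cut-offs of 20, 28 and 24.

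**The concern.** The Phase III rule resembles the one for the Phase I nominal group, where a moderator leads a discussion and either language can work. In Phase III the participant must read, alone, first an app and then a questionnaire, both in Malay. The eligibility rule does not match the study materials.

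Three things are at stake:

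- **Validity of the score.** The protocol defines ease of use partly through understanding the app, so a reader's language ability enters that domain directly. The validation it reports is of the Malay translation, and answers from someone who cannot read that translation fall outside it.
- **The feedback to the developer.** Phase III results guide changes before the final prototype. Low ratings that come from language could be taken for interface faults.
- **Avoidable loss.** A caregiver who finds the app or form unreadable may leave after being enrolled.

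None of this can be separated out afterwards, because no language variable is described.

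**Working it through.** **1. Who is eligible under Table 2**

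| Caregiver | Excluded by the language rule? | Reads app and M-MAUQ? |
|---|---|---|
| Reads Malay | No | Yes |
| English only | No | No |
| Speaks but does not read Malay | No | No |
| Communicates in neither language | Yes | No |

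The second and third rows are the mismatch. The sentence could be stretched to mean that lacking either language excludes. That would turn away Malay-only caregivers from a Malay app, and it would still test communication and not reading, so it does not repair the rule.

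**2. The plan's own figures**

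- Cut-off: 18 items × 4 = 72, on a range of 18 × 1 = 18 to 18 × 7 = 126.
- Domains: 5 × 4 = 20, 7 × 4 = 28, 6 × 4 = 24.
- Sample: 18 × 5 = 90, and 90 × 1.2 = 108 invited.

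All reproduce the stated values and are not in dispute here.

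**3. Possible shift in the mean total, on assumed inputs**

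The documents give neither the share *s* of respondents who do not read Malay nor their score deficit *d*. Assume *s* = 5–10% and a deficit of 1–2 points per item, so *d* = 18–36. Shift = *s* × *d*:

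| | *d* = 18 | *d* = 36 |
|---|---|---|
| *s* = 0.05 | 0.9 | 1.8 |
| *s* = 0.10 | 1.8 | 3.6 |

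The largest value is 3.6 / (126 − 18) = 3.3% of the score range. It would change the conclusion only if the mean without this effect lay from 72 up to 75.6.

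**4. Share needed to bring the mean down to 72**

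Let Malay readers average *m* per item and non-readers *l*, both assumed. The tipping share is (*m* − 4)/(*m* − *l*):

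| | *l* = 1 | *l* = 2 | *l* = 3 |
|---|---|---|---|
| *m* = 4.2 | 0.2/3.2 = 6% | 0.2/2.2 = 9% | 0.2/1.2 = 17% |
| *m* = 5.0 | 1/4 = 25% | 1/3 = 33% | 1/2 = 50% |

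The effect runs from negligible to decisive, depending wholly on inputs that the documents do not contain.

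**5. Direction**

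Low scores are one possibility. If non-readers instead guessed evenly over 1 to 7, their item mean would be (1 + 7)/2 = 4, a total of 72. That pulls the overall mean towards the cut-off without carrying it across. The direction is therefore not fixed either.

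**The case against.** The strongest reply accepts the mismatch and disputes its weight.

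- **Few may be affected.** The app is in the national language, and nothing shows that caregivers without Malay literacy are a material share at the two sites. This stands.
- **They may never be scored.** Such a caregiver would have to consent, install a Malay app, keep it for four to six weeks and then submit the form. Compulsory items block partial forms but compel nobody to submit. Loss is at least as plausible as invalid scores, and the plan already allows 20% for non-response. This stands, but loss caused by the eligibility rule is avoidable.
- **Low scores would count against the app.** They would not create a false claim of good usability. This holds if scores are indeed low. A misleading signal to the developer would remain.
- **Difficulty with a Malay-only app is partly a usability finding.** The objective concerns dementia caregivers generally. That is fair for the app. It does not excuse measuring these caregivers with a questionnaire they cannot read.
- **The study is descriptive.** It has one group, a mean and SD, and no hypothesis test. This limits the severity.

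A reader might infer that Phase III scores will measure a language barrier instead of usability. The documents do not support that. It could concern only a subset of unknown size, and for those who respond, comprehension would be mixed with usability and would not replace it.

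**Conclusion.** The point holds as a mismatch between a stated eligibility rule and stated study materials. It is a wrongly set rule, not a detail left to a fuller document, because Table 2 sets out the Phase III criteria explicitly and nothing elsewhere adds a Malay-reading requirement or an English version.

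The mismatch is certain; its effect is not. For any participants who do not read Malay, M-MAUQ scores may confound comprehension with usability, or the participants may be lost. The 0.9 to 3.6 points and the tipping shares of 6% to 50% rest on assumed shares and scores and are only illustrative. They do not show that the conclusion at 72 would change. Should-fix.

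**What to change.** In Table 2, replace the Phase III language exclusion with: *not able to read and understand Bahasa Malaysia*. State briefly how this is judged at screening, since reading ability is graded. Keep English or Malay for the Phase I nominal group.

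The edit is one line before Phase III enrolment, submitted to the ethics committee as the protocol requires for modifications. Its cost is a slightly smaller and somewhat less linguistically diverse pool, which works a little against the Discussion's wish for a varied sample, and the usability conclusion is then limited to caregivers who read Malay.

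If caregivers without Malay literacy are meant to be part of the target group, the consistent alternative is an English app and a validated English questionnaire, with results reported by language. That is much more work. Recording reading proficiency and reporting by it would expose the problem, but it would not make a Malay form valid for people who cannot read it.

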## Data Availability

The data presented in this study will be available on request from the corresponding author.
